### **5.5. Sensitivity analyses**

The analysis of prostate cancer mortality will be repeated, but with the outcome defined as death definitely, probably **and possibly** due to prostate cancer.

## **6. 15-YEAR PUBLICATION PLAN**

### **6.1. Planned papers and timelines**

The intention is to present the clinical and patient-reported outcomes in a pair of papers, to be submitted to a high impact medical journal by late 2021. With a census date of **23rd November 2020** for clinical outcomes contributing to this analysis, this will allow those routine data available by 30th June 2021 to be incorporated.

## 7. FINAL REPORT TABLES AND FIGURES

**Figure 1.** CONSORT flowchart, illustrating the flow of participants through each of the three arms of the trial, from the point of randomisation.

[figure not shown]

**Figure 2.** Kaplan-Meier estimates of the cumulative probability of undergoing radical interventions during the follow-up period, according to treatment group.

Radical intervention was defined as a radical prostatectomy, per-protocol radiotherapy, non-protocol radiotherapy (including brachytherapy), or high-intensity focussed ultrasound therapy.

**Figure 3.** Kaplan-Meier estimates of prostate cancer-specific survival and freedom from disease progression, according to treatment group: active monitoring (solid line), surgery (long dash line) and radiotherapy (short dash line) treatment groups

Panel A shows the rate of prostate cancer-specific survival. Prostate cancer-specific deaths were those that were definitely or probably due to prostate cancer as determined by an independent cause-of-death evaluation committee whose members were unaware of treatment assignments.

Panel B shows the rate of overall survival.

Panel C shows the rate of freedom from disease progression. Clinical progression of prostate cancer included metastases and death due to prostate cancer or its treatment.

**Table 1.** Prostate cancer mortality, Clinical progression, metastatic disease and all-cause mortality, by randomised group

|                                                                     | Active monitoring protocol
(N=545) | Surgery
(N=553) | Radiotherapy protocol
(N=545) | p-value  |
|---------------------------------------------------------------------|---------------------------------------|--------------------|----------------------------------|----------------------|
| Total person years in follow-up                                     |                                       |                    |                                  |                      |
| Number of deaths due to prostate cancer                 |                                       |                    |                                  |                      |
| % prostate cancer mortality at median 10 years (95% CI)             |                                       |                    |                                  |                      |
| % prostate cancer mortality at median 15 years (95% CI)             |                                       |                    |                                  |                      |
| Prostate cancer deaths  per 1000 person years (95% CI)  |                                       |                    |                                  |                      |
| Number of deaths due to any cause                                   |                                       |                    |                                  |                      |
| All-cause deaths per 1000 person years (95% CI)                     |                                       |                    |                                  |                      |
| Person years of follow-up free of hormone treatment                 |                                       |                    |                                  |                      |
| Number of men treated with hormones for advanced disease            |                                       |                    |                                  |                      |
| Starting hormone treatment per 1000 person years (95% CI)           |                                       |                    |                                  |                      |
| Person years of follow-up free of clinical progression  |                                       |                    |                                  |                      |
| Number of men with clinical progression                             |                                       |                    |                                  |                      |
| Clinical progression per 1000 person years (95% CI)                 |                                       |                    |                                  |                      |
| Person years of follow-up free of metastatic disease                |                                       |                    |                                  |                      |
| Number of men with metastatic disease                               |                                       |                    |                                  |                      |
| Metastatic disease per 1000 person years (95% CI)                   |                                       |                    |                                  |                      |

 Likelihood ratio test of the null hypothesis “no difference in prostate cancer mortality between the three treatment arms”, adjusted for study centre, age, mean PSA at prostate check clinic and biopsy, and Gleason score at baseline. Death probably or definitely due to prostate cancer or its treatment as judged by an independent committee. Disease progression includes evidence of metastatic disease; the initiation of hormone therapy; diagnosis of clinical T3 or T4 disease; or ureteric obstruction, rectal fistula, or the need for a permanent catheter when these are not considered to be a complication of treatment.

**Table 2.** Prostate cancer deaths by randomised group and subgroup

|                                                    | Rate prostate cancer mortality  per 1000 person years
(number of deaths) |                    |                                  | p-value  |
|----------------------------------------------------|-----------------------------------------------------------------------------------------|--------------------|----------------------------------|----------------------|
|                                                    | Active monitoring
protocol (N=545)                                                   | Surgery
(N=553) | Radiotherapy
protocol (N=545) |                      |
| Age at randomization                               |                                                                                         |                    |                                  |                      |
| < 65 years                                         |                                                                                         |                    |                                  |                      |
| 65 years+                                          |                                                                                         |                    |                                  |                      |
| Grade group at diagnosis                           |                                                                                         |                    |                                  |                      |
| Group 1                                            |                                                                                         |                    |                                  |                      |
| Group 2                                            |                                                                                         |                    |                                  |                      |
| Group 3+                                           |                                                                                         |                    |                                  |                      |
| Aggregate tumour length in
biopsy cores         |                                                                                         |                    |                                  |                      |
| <4mm                                               |                                                                                         |                    |                                  |                      |
| 4mm+                                               |                                                                                         |                    |                                  |                      |
| Maximum tumour length in any
single biopsy core |                                                                                         |                    |                                  |                      |
| <2mm                                               |                                                                                         |                    |                                  |                      |
| 2mm+                                               |                                                                                         |                    |                                  |                      |
| PSA level at diagnosis                             |                                                                                         |                    |                                  |                      |
| < 10 ng/ml                                         |                                                                                         |                    |                                  |                      |
| 10 ng/ml+                                          |                                                                                         |                    |                                  |                      |
| Clinical stage at diagnosis                        |                                                                                         |                    |                                  |                      |
| T1c                                                |                                                                                         |                    |                                  |                      |
| T2                                                 |                                                                                         |                    |                                  |                      |
| CAPRA risk score                                   |                                                                                         |                    |                                  |                      |
| Low risk (score 0-1)                               |                                                                                         |                    |                                  |                      |
| Medium / high risk (score >1)                      |                                                                                         |                    |                                  |                      |
| D'Amico risk group                                 |                                                                                         |                    |                                  |                      |
| Low                                                |                                                                                         |                    |                                  |                      |
| Intermediate / high                                |                                                                                         |                    |                                  |                      |

Death probably or definitely due to prostate cancer or its treatment as judged by an independent committee. Likelihood ratio test of the null hypothesis “equal relative treatment effects across the subgroups”, adjusted for study centre, age, mean PSA at prostate check clinic and biopsy, and Gleason score at baseline.

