**This treatment protocol is to be given to participants either randomised to or selecting a particular treatment.**

### 20.1 Treatment Details

All participants will receive neoadjuvant hormone therapy for 3-6 months followed by external beam radiotherapy using 3D conformal methods. Participants will not be eligible to receive prostate brachytherapy, either as sole treatment or as a boost following external beam treatment.

Neo-adjuvant Androgen Deprivation will be achieved in all patients using LHRH agonists at four weekly cycles in conjunction with initial Cypoterone Acetate (CPA) or equivalent alternative, to prevent "flare phenomenon". The CPA or equivalent should commence approximately one week prior to the first LHRH agonist injection and should be given for a total of at least three weeks. The duration of Androgen Deprivation

should be at least three months and a maximum of six months, prior to commencement of radiotherapy and should continue until the end of radiotherapy.

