### **The Number of Participants**

The original sample size calculation was presented in published protocol. The ProtecT study randomly allocated 545 men to active monitoring, 553 men to surgery, and 545 men to radiotherapy. Amongst these men, at median 10-year follow-up, there were 8, 5 and 4 prostate cancer deaths respectively. There were very few withdrawals at the time of the median 10-year analyses in randomised men. A simple extrapolation from the occurrence of prostate cancer deaths during the median 10-year follow-up, suggests that by the end of 2020 the number will have doubled from 17 to 34 among those randomised. If there is an increase in the incidence rate of prostate cancer death, as may result from the number of metastatic disease cases that have been diagnosed, then conditional power of 67%, 78%, and 85%, would result from the occurrence of 48, 60, and 72 prostate cancer deaths respectively.

A formal sample size calculation was not undertaken for men in other groups (advanced cancer, comorbidities or with and initial PSA of 20ng/ml or above). All men in these groups will be followed up observationally.

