## 2.5. Description of interventions

The **Active Monitoring Protocol** aimed to avoid immediate radical treatment whilst assessing the disease over time, with a review and the opportunity for radical treatment if there was evidence of disease progression. PSA levels were measured and reviewed every three months in the first year and twice yearly thereafter. Changes in PSA levels were assessed, and a rise of at least 50% over the previous 12 months triggered repeat testing within six to nine weeks. If the PSA levels were persistently raised, or the patient had other concerns, a review appointment was made to consider treatment options.

The **Radiotherapy Protocol** began with neoadjuvant androgen suppression, given for three to six months before and concomitantly with 3D-conformal radiation therapy delivered at 74 Gy in 37 fractions.

**Surgery** was a radical retropubic prostatectomy procedure. The surgical approach was left to the discretion of the surgeon, and was most commonly open, but laparoscopic, or robot-assisted approaches were permitted from 2003.

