### 2.9.2. Secondary outcomes

*Secondary clinical and patient-reported outcomes to be presented in the 15-year results papers are:*

- *overall mortality*

- *metastatic disease*
- *clinical disease progression*
- *initiation of long-term hormone therapy*
- *patient reported outcomes (PROMs)*

*Metastatic disease is defined as positive imaging showing bony, visceral and/or lymph node metastases, or PSA above 100; or bone marrow infiltration with associated systemic symptoms.*

*Clinical disease progression will be measured as person-years free of the consequences of disease progression. Signs of disease progression will include evidence of metastatic disease; the initiation of long-term hormone therapy; diagnosis of clinical T3 or T4 disease; or ureteric obstruction, rectal fistula, or the need for a permanent catheter when these are not considered to be a complication of treatment. There will be a review of cases where disease progression or metastatic disease are uncertain.*

As the ascertainment of clinical disease progression may differ between the three study arms, we will also present the initiation of long-term hormone therapy, to indicate those men whose disease is no longer curable.

The reporting of metastatic disease, clinical disease progression, and initiation of long-term hormone therapy is conditional on securing the data.

*The patient-reported outcomes which have been measured are listed in the Appendix. These measures are derived from validated questionnaires and have been completed at recruitment, at first biopsy, six months after randomisation, and yearly thereafter. These measures will be reported in a separate companion paper, to be submitted for publication at the same time as the primary outcomes paper.*

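### The 15-year SAP defines clinical progression inconsistently: Table 1 footnote 3 drops the long-term limit on hormone therapy, and Figure 3C names a death component that the other two places do not list

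*Supplement*

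**What the plan says.** The current analysis plan is the 15-year SAP of November 2020. It describes clinical progression in three places.

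- Section 2.9.2 (Secondary outcomes) lists metastatic disease, then "the initiation of long-term hormone therapy; diagnosis of clinical T3 or T4 disease", then ureteric obstruction, rectal fistula or a permanent catheter when not a treatment complication. Death is not in the list. The same section makes hormone initiation a separate outcome, "to indicate those men whose disease is no longer curable".
- Section 7, Table 1, footnote 3 is attached to the clinical progression rows: "Disease progression includes evidence of metastatic disease; the initiation of hormone therapy; diagnosis of clinical T3 or T4 disease". The rest matches section 2.9.2, and death is again not listed.
- Section 7, Figure 3, Panel C: "Clinical progression of prostate cancer included metastases and death due to prostate cancer or its treatment".

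Table 1 also has three hormone rows. The count row is "Number of men treated with hormones for advanced disease". The person-years row and the rate row refer to hormone treatment with no such limit.

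On treatment, SAP section 2.5 says that the radiotherapy protocol "began with neoadjuvant androgen suppression, given for three to six months before and concomitantly with 3D-conformal radiation therapy". Section 20.1 of the protocol (version 5.5) says: "All participants will receive neoadjuvant hormone therapy for 3-6 months followed by external beam radiotherapy using 3D conformal methods".

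**The concern.** The footnote is the definition printed against the progression counts, person-years and rates, so it is the one a reader or a second analyst will apply. Without the long-term limit, it makes the first step of one randomised treatment an outcome event. The resulting misclassification would depend on arm, and it would contradict the purpose that section 2.9.2 gives for looking at hormone therapy at all.

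There is also a smaller problem. The curve in Panel C and the numbers in Table 1 carry one name but may not count the same events, because only the caption names death.

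Section 1 of the SAP says that the plan should let others perform or replicate the analysis. Conflicting definitions of a named outcome work against that.

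**Working it through.** The plan gives no figure to reproduce here, so the check sets the wordings side by side and then sizes the literal reading.

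**1. The three wordings.** All name metastatic disease. They differ as follows.

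| Place in 15-year SAP | Hormone item | T3/T4 and local items | Death from prostate cancer or its treatment |
|---|---|---|---|
| Section 2.9.2 | long-term only | named | not named |
| Table 1, footnote 3 | any initiation | named | not named |
| Figure 3, Panel C | not named | not named | named |

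**2. What the footnote does if read literally.** Androgen suppression is given to all who receive the radiotherapy protocol (SAP 2.5, protocol 20.1). Each such man initiates hormone therapy before his first fraction and so meets footnote 3. This applies to men allocated to radiotherapy who start the protocol, to active-monitoring men who later take it up, and to surgery-allocated men who cross over to it.

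**3. Size of the literal reading.**
- Men allocated: the trial "randomly allocated 545 men to active monitoring, 553 men to surgery, and 545 men to radiotherapy" (protocol Appendix 2, The Number of Participants).
- Share starting the allocated treatment: 75% to 85%. This is the assumption in protocol Appendix 2 for the precision of an on-treatment analysis. It is not observed radiotherapy uptake, which the documents do not give.
- Counted as progressed at treatment start = share × 545: 0.75 × 545 = 408.75, about 409; 0.85 × 545 = 463.25, about 463. The ceiling is 545, if every allocated man starts.
- Under section 2.9.2, with long-term read as its stated purpose implies, the number counted for this reason is 0.

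**4. Is restoring the missing word enough?** The SAP gives long-term no duration, no indication and no exclusion. Under protocol 20.1, suppression runs three to six months before radiotherapy and continues to its end. Protocol 20.8 plans 7.4 weeks of treatment, which is 7.4 × 7 / 30.4 = 1.7 months. The course therefore lasts from 3 + 1.7 = 4.7 months to 6 + 1.7 = 7.7 months. A six-month rule, taken purely as an example that no document proposes, would still catch the longer courses. The exclusion has to be stated, not left to the adjective.

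**5. The hormone rows.** The count is limited to advanced disease. The person-years free of hormone treatment, read as written, stop at any hormone start. A man on the radiotherapy protocol would then leave the denominator early without being able to enter the numerator on that account.

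**6. The death component.** A man who dies of prostate cancer or its treatment with no earlier listed sign is named as an event in Panel C only. The gap between curve and table cannot exceed the number of such deaths. Protocol Appendix 2 gives 8 + 5 + 4 = 17 prostate cancer deaths at the median 10-year analysis and a simple extrapolation to 34 by the end of 2020. The actual gap should be well below that, since most of these deaths would presumably follow metastasis or hormone treatment.

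**The case against.** The strongest reply is that section 2.9.2 is where outcomes are defined, and it settles the intent. Neoadjuvant suppression given with curative radiotherapy is plainly not a marker of incurable disease. The footnote sits in an empty table shell and repeats the wording of the 2015 SAP (section 2.10.2 and Table 4), so it looks like text not updated when section 2.9.2 was revised. An analyst who follows section 2.9.2 would not make the error. All of this stands. It makes the correction uncontroversial, but it does not remove the conflict from the latest plan.

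Other points also limit the finding:
- All three texts use a form of *include*, so none is strictly exhaustive, and the Panel C caption may be shorthand.
- The advanced-disease row belongs to the separate hormone outcome. It is not another definition of progression, and it supports the section 2.9.2 reading.
- Initial radiotherapy courses had their own data schedules (protocol 22.5), so reliance on routine data matters mainly for later switchers. Section 2.9.2 also provides a review of uncertain cases, although a review does not choose between definitions.

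A reader might infer that the plan will in fact score the whole radiotherapy arm as progressed. The documents do not support that: only the literal footnote leads there, and only for men who start the protocol. A reader might also infer that the surgery arm is untouched. That is not supported either, since surgery-allocated men may cross over, and protocol 19.4 allows adjuvant hormonal manipulation after positive margins.

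**Conclusion.** The inconsistency is real and goes beyond a slip of wording, because the footnote defines the reported progression rows and long-term is nowhere defined so as to exclude the radiotherapy course. Taken literally, the footnote would misclassify about 409-463 of 545 men in the radiotherapy arm. That rests on a 75-85% planning range and on a reading that section 2.9.2 contradicts, so it shows what is at stake and is not a forecast. The bias would fall mainly on the radiotherapy arm and on men who switch to radiotherapy. The mismatch over death is probably small and cannot be sized from the documents beyond the ceiling shown.

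The point concerns a secondary outcome, and section 2.9.2 makes its reporting conditional on securing the data. The primary outcome, prostate cancer mortality, does not depend on it.

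**What to change.** Use one definition of clinical progression in section 2.9.2, Table 1 footnote 3 and Figure 3 Panel C, and one hormone event in all three hormone rows of Table 1:

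1. Carry the long-term qualifier into footnote 3 and into the hormone count, person-years and rate rows.
2. State, as an analysis rule, that androgen suppression given as part of a radical radiotherapy course is not an event, whatever arm the man was allocated to.
3. State once whether death from prostate cancer or its treatment is a component of progression, and apply the answer to both the table and the curve.

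The cost is a few lines of SAP text and one derivation rule that links hormone start dates to radiotherapy dates. Whether those dates are complete for late switchers is not confirmed in the documents. Protocol section 3.1 indicates that 15-year results were in hand by January 2022, and Appendix 2 says that the 20-year analyses will follow similar approaches. The 15-year report should therefore say which definition was applied, and the corrected wording should go into the 20-year plan.
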